## Method

### Study design

This is a non-interventional and parallelised study with a matched control group. The study was conducted monocentrally at the out-patient and day patient department of the Clinic of Child and Adolescent Psychiatry, Psychosomatics and Psychotherapy at the University of Regensburg, Germany. We choose the out-patient and day patient department to reduce sleep disturbance from the hospital environment or shared rooms expected for those patients admitted to hospital. By choosing a patient cohort that sleeps in their usual surroundings without external influences, we aim to focus on changes in sleep quality that can be attributed to the depressive disorder.

The study protocol conforms to the Standard Protocol Items: Recommendations for interventional Trials (SPIRIT) checklist.

### Ethics approval and consent to participate

The authors assert that all procedures contributing to this work comply with the ethical standards of the relevant national and institutional committees on human experimentation and with the Helsinki Declaration of 1975, as revised in 2008. All procedures involving human patients were approved by the ethics committee at the University of Regensburg. The committee consented to study execution on 19 February 2020, and the reference number is 20-1711-101.

Before any data was gathered, written informed consent was obtained from all participants and their legal guardians. Voluntary participation is mandatory and withdrawal from the study is possible at any time. Saliva samples given to the external laboratory for analysis are submitted, numbered and without any possibility of allocation.

This study is registered with the German Clinical Trials Register; the date of registration was 8 April 2020 and the registration number is DRKS00020907.

### Eligibility criteria

Eligibility criteria are screened twice before study participation: initially in the first contact via telephone, and a second time immediately before study participation at the first study appointment (eligibility screen, see Fig. 1).

**Fig. 1 fig01:**
[figure not shown]
Study schedule. BAI, Beck Anxiety Inventory; BDI-II, Beck Depression Inventory-II; M.I.N.I KID 6.0, Mini-International Neuropsychiatric Interview for Children and Adolescents; PDS, Pubertal Development Scale; SF-A/R, Sleep Questionnaire A – revised version; SF-B/R, Sleep Questionnaire B – revised version; SSKJ 3-8 R, Questionnaire for the Measurement Stress and Coping in Children and Adolescents – revised version.

#### Inclusion criteria

Children and adolescents between 12 and 18 years are eligible for participation. A sufficient understanding of the German language, as well as informed consent of both participants and legal guardians, is required to participate in the study.

For the index group, potential participants are those with depressive disorders according to the diagnostic criteria of the ICD-10.^33^ More precisely, we include the ICD-10 codes F32.0 (mild depressive episode), F32.1 (moderate depressive episode), F32.2 (severe depressive episode without psychotic symptoms), F33.0 (major depressive disorder, recurrent, mild), F33.1 (major depressive disorder, recurrent, moderate), F33.2 (major depressive disorder, recurrent, severe without psychotic features) and F43.21 (adjustment disorder with prolonged depressive reaction) in our index group.

For the control group, we include healthy adolescents matched by gender, age and pubertal status according to the Pubertal Development Scale (PDS). This shall align age- and gender-specific differences.^34^

#### Exclusion criteria

Potential participants who suffer from psychotic or acute suicidal conditions are excluded from study participation. Pregnancy, antidepressant or glucocorticoid medication, and neurological or endocrinological illnesses that may affect brain physiology or relevant endocrinological parameters are additional exclusion criteria. Moreover, those with cannabis consumption within the 3 months before study participation are excluded.

Furthermore, most psychiatric comorbidities constitute exclusion criteria. For the index group, we include anxiety disorders, as they appear cumulatively comorbid with depressive disorders.^35,36^ All other psychiatric comorbidities lead to exclusion.

For the control group, we exclude participants with any psychiatric disease, symptoms indicating a current psychiatric disease, a history of psychotherapeutic or psychiatric intervention, or a condition requiring therapeutic support. Potential participants excluded because of the latter criterion are offered therapeutic help if the indication is given.

### Recruitment

In the index group, participants with a diagnosed depressive disorder are consecutively recruited from the patient cohort of the out-patient department and day patient department of the Clinic of Child and Adolescent Psychiatry, Psychosomatics and Psychotherapy at the University of Regensburg, Germany.

To recruit healthy adolescents for the control group, we will announce the study and call for participation via mailing lists, websites and social media channels of our hospital.

In case of drop-out, recruitment will be continued using the abovementioned resources until the intended number of participants is achieved.

### Informed consent

No participant is included in the study unless written informed consent of the participants and legal guardians is given. If consent is revoked at any point during or after participation, all examinations of this study will be cancelled immediately for this participant.

### Measurements

#### Assessment of depressive symptoms, psychiatric comorbidities and stress responsiveness

Initially, all participants are screened and interviewed with the Mini-International Neuropsychiatric Interview for Children and Adolescents (M.I.N.I. KID 6.0)^37^ for psychiatric disorders (controls) or comorbidities (patients) (T1, see Fig. 1). The M.I.N.I. KID 6.0 interview is structured into 24 diagnostic modules assessing potential symptoms of psychiatric disorders according to the DSM-IV and ICD-10.

Depressive symptoms are assessed via the Beck Depression Inventory-II,^38^ which is one of the most commonly used self-rating scales to measure depressive symptoms^39^ from the age of 13 years (T1, see Fig. 1). Frequently observed symptoms are inquired for the past 2 weeks in 21 items, with four possible response options covering increasing symptom severity. As an adjustment for the younger study participants, we excluded item 21 (loss of interest in sexuality) in our assessment. Internal consistency for the German version is good (*α* ≥ 0.84), retest reliability is *r* ≥ 0.75 and discriminative validity is confirmed.^40^ The applicability to an adolescent sample was checked and validated.^41,42^

As symptoms of anxiety and anxiety disorders occur often concurrently with depressive disorders,^35,36^ we examine anxiety via the Beck Anxiety Inventory (BAI)^43^ (T1, see Fig. 1). The BAI consists of 21 items focusing on somatic symptoms of anxiety experienced within the past week.^44^ The German BAI showed reliable and valid psychometrics.^45^ For adolescent samples, the BAI showed at least acceptable psychometric properties in other language versions.^45,46^

Stable sleeping habits and needs will be assessed by a short self-designed self-report survey (T1, see Fig. 1). This survey assesses chronotype, the regularity of bedtimes, the duration of sleep needed to feel rested and the frequency of sleeping through school or work. Furthermore, it queries the usual bed and wake-up times for each school/working days and weekend days/holidays. The items used for this survey are based on the Sleep Habit Survey (SHS).^47^ For the subscales, the original SHS showed acceptable internal consistency, with *α* ranging from 0.70 to 0.79.^48^

Participants with a depressive disorder additionally answer a self-designed questionnaire examining potential differences in relevant aspects of sleep quality since the onset of depressive symptoms (T1, see Fig. 1). This questionnaire consists of eight items, in which the participants compare the need to sleep, sleep and dream quality, WASO, mood at awakening, time of awakening and personal relevance of the topic sleep before and after symptom onset, and evaluate changes on a five-point Likert scale.

Sleeping quality of the previous 2 weeks is evaluated with the Sleep Questionnaire B (SF-B/R)^49^ (T1, see Fig. 1). The SF-B/R is a validated 31-question survey. Five sleep indices can be calculated: difficulty falling asleep, difficulty staying asleep, premature awakening, general sleep characterisation and total sleep duration. In addition, seven factor scales (sleep quality, feeling of being refreshed after sleep, mental balance before sleep, feeling mentally exhausted before sleep, psychosomatic symptoms during the sleep phase, dream recall and sleep–wake regulation) can be assessed. The SF-B/R is designed for sleep research as well as clinical practice. Satisfactory reliability values >0.70 are shown with regard to the internal consistency of the factor levels and the retest reliability of the SF-B/R (2–4 weeks). With regard to convergent validity, medium correlations are found with construct-related domains, such as measures of well-being, depression and personality factors.^49^

Participants also complete the Stress and Coping Questionnaire for Children and Adolescents (SSKJ 3-8 R)^50^ (T1, see Fig. 1). The SSKJ 3-8 R is a self-report questionnaire based on the transactional model of stress and coping developed by Lazarus and Folkman, assessing several strategies to reduce negative emotions or to change conditions in problematic or negatively experienced situations.^51^ The first part comprises an assessment of vulnerability to different stressors on four-level visual analogue scales. The second part includes five- and three-point Likert scales evaluating the usage frequency of five different coping strategies.^51^ The German version of the SSKJ 3-8 R showed sufficient reliability and validity has been confirmed.^52,53^

Pubertal development is assessed with the use of the German adaption^54^ of the Pubertal Development Scale (PDS)^55^ as a self-report questionnaire (T1, see Fig. 1). Female participants asses the current status of breast development, pubic hair growth, growth in height and skin, and estimated level of development compared with peers. Male participants are asked to evaluate the start and level of beard growth, existence of puberty vocal changes, pubic hair growth, growth in height, and skin changes, and to compare their level of development with their peers.^54,55^ Measures of criterion validity as well as internal consistency have achieved acceptable values.^54^

#### Accelerometry

For sleep measuring, we use the ActTrust 2 wrist actimeter (Condor Instruments) worn on the non-dominant wrist for seven consecutive nights, starting on Sunday evening (measurement week, see Fig. 2). Wearing and handling of this accelerometer is practiced by the adolescents and their legal guardians during the first study appointment. During the measurement week, participants put on the accelerometer when they go to bed in the evening. By pushing the event button, they record the time they intend to sleep and mark unexpected events or delays (for example, getting up again to go to the bathroom). While sleeping, data is recorded in 1-min intervals. The selected interval is the default of the manufacturer Condor Instruments, and is obligatory for the post-processing of sleep data. In the morning, wake-up time is recorded by pushing the event button again. Having marked the wake-up time, participants take the accelerometer off.

**Fig. 2 fig02:**
[figure not shown]
Study diagram. BAI, Beck Anxiety Inventory; BDI-II, Beck Depression Inventory-II; CAR, cortisol awakening response; M.I.N.I KID 6.0, Mini-International Neuropsychiatric Interview for Children and Adolescents; PDS, Pubertal Development Scale; SF-A/R, Sleep Questionnaire A – revised version; SF-B/R, Sleep Questionnaire B – revised version; SSKJ 3-8 R, Questionnaire for the Measurement Stress and Coping in Children and Adolescents – revised version.

After participants return the accelerometer at the second study appointment, we check the recordings with the ActStudio software (Condor Instruments, São Paulo, Brazil, PC version 1.0.10, for Windows; see https://www.condorinst.com.br/en/actstudio-software/). In accordance with the standard procedure in sleep accelerometry, we manually identify the main sleep period.^56^ Bed time, get up time, time in bed, total sleep time, onset latency, sleep efficiency, WASO, awakenings and the intensity of blue light are provided by the software. Additionally, activity data during sleep is derived from the data, as increased motor activity is associated with impaired sleep quality.^9^

In the validation study, the ActTrust accelerometer achieved satisfactory results with a sensitivity of 95.69%, a specificity of 30.59%, an accuracy of 80.24%, a predictive value for sleep of 81.52% and a predictive value for wakefulness of 68.93%.^57^ Regarding the correlation analysis between accelerometry and polysomnography, *r* = 0.491 (*P* < 0.001) was observed for total sleep time, *r* = 0.499 (*P* < 0.001) for wake after sleep onset, *r* = 0.345 (*P* < 0.001) for sleep efficiency and no statistical significance was observed for sleep onset latency.^57^

#### Daily sleep questionnaires

To examine subjective sleep quality, participants complete a short questionnaire including 11 items, each morning after accelerometry measurements (measurement week, see Fig. 2). Participants evaluate the satisfaction with the past night's sleep, current mood and feelings of recreation, difficulties with sleeping in nocturnal awakening and stress level of the past day, on a six-point Likert scale. Information on the presence of nightmares, the consumed quantity of caffeinated beverages and the consumed quantity of alcoholic beverages will be gathered. Additionally, the questionnaire assesses sleeping and wake-up time to double check the ActTrust recordings.

On the last morning of measurements, participants answer the daily questionnaire as well as the Sleep Questionnaire A (SF-A/R)^49^ (measurement week, see Fig. 2). The SF-A/R includes 25 questions assessing several qualitative and quantitative aspects of the past night's sleep. Similarly to the SF-B/R, sleep indices and factor scales can be calculated. We use data from both questionnaires to compare measurements of the self-designed daily sleep questionnaire with a standardised sleep survey.

#### Saliva sampling

To analyse the CAR and the course of alpha-amylase after awakening, saliva samples are collected. We instruct participants to collect saliva samples via Salivette Cortisol (Sarstedt, Nümbrecht, Germany; item number 51.1534.500) devices on three consecutive weekdays (Tuesday to Thursday) at three time points (measurement week, see Fig. 2). The first sampling time is immediately after awakening (base level of CAR), the second sample is collected 30 min after awakening (peak in CAR) and the last sampling time is 45 min after awakening (decrease in CAR). The chosen time intervals conform to the recommended sampling points of the expert consensus guidelines for CAR.^32^

At predetermined times, participants open a container equipped with a medication event monitoring system cap that records the opening time. The Salivettes are equipped with the fitting label for sampling days and time. Participants are instructed in oral and written form not to eat, drink or brush their teeth for 10 mins before collecting saliva samples.

The Salivettes are coded with weekdays and corresponding colours, and are kept separate for each weekday, to maximise clarity and simplify saliva sampling for participants. Sampling times are recorded and participants are informed about the monitoring before the implementation of measurements.

After sample collection, participants store the samples in their fridge or freezer, and return the samples on the second study appointment (T2, see Fig. 2). Then, the saliva samples are stored transitionally in the institute's freezer at −20°C. After completion of the study, the saliva samples are sent with a pseudonymised labelling to the Laboratory of the Department of Biopsychology, Technical University of Dresden, Germany, for analysis.

### Physiological consistency of measurement

As all participants start measurements on a Sunday evening, the weekdays of accelerometry and saliva sampling stay constant over all participants. Measurement timing of female participants is aligned with the female menstrual cycle. Start of the most recent menstruation is assessed at the first study appointment, and all measurements are scheduled for the female participants’ luteal phase, as previous studies found evidence that CAR between women and men might be most similar during the luteal phase.^58,59^ Moreover, use of oral contraceptives is assessed, as this may slightly blunt the CAR.^60^

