### Trial status

Recruitment has started on 1 February 2021, and the study is intended to be completed by February 2022.

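### A fixed weekday does not equalise term and holiday mornings, and nothing stated balances week type between patients and controls

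*Protocol article*

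**What the plan says.** All references are to the Protocol article.

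- **Weekday rule** (Physiological consistency of measurement): "As all participants start measurements on a Sunday evening, the weekdays of accelerometry and saliva sampling stay constant over all participants". Accelerometry runs "for seven consecutive nights, starting on Sunday evening" (Accelerometry), and saliva is collected "on three consecutive weekdays (Tuesday to Thursday) at three time points" (Saliva sampling).
- **Only other timing rule** (same section): "all measurements are scheduled for the female participants" in the luteal phase.
- **Calendar span** (Trial status): "Recruitment has started on 1 February 2021, and the study is intended to be completed by February 2022".
- **Habitual schedule** (Assessment of depressive symptoms, psychiatric comorbidities and stress responsiveness): the baseline sleep survey is said to cover both regimes: "it queries the usual bed and wake-up times for each school/working days and weekend days/holidays".
- **How the groups arise** (Recruitment): "participants with a diagnosed depressive disorder are consecutively recruited from the patient cohort of the out-patient department and day patient department". Controls answer announcements on mailing lists, websites and social media. Inclusion criteria gives gender, age and pubertal status as the matching factors.
- **Aim** (Study design): "By choosing a patient cohort that sleeps in their usual surroundings without external influences", the article intends to focus on sleep changes attributable to the depressive disorder.
- **Analysis** (Statistical analysis): the hormone ANCOVAs have group as the independent variable, and no covariate is named.

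**The concern.** A constant weekday makes mornings comparable only if a given weekday imposes the same obligations on everyone. For adolescents it does not. In term, the hour of waking is set by school; in the holidays it is largely free. The baseline survey shows that the authors regard these as different regimes, yet the scheduling rule does not distinguish them.

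The groups could differ in week type for reasons unrelated to depression. Patients enter as they present to the clinic, whereas controls volunteer when they see a call and have time. Nothing stated ties a control's week to that of the matched patient. At stake is the attribution to depression that the design is meant to allow. An imbalance could create or mask a group difference in the sleep measures or the awakening response.

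**Working it through.** **No figure in the plan is at issue**, so there is none to reproduce. The check is how far the stated rule leaves week type open, and what an imbalance would do under stated assumptions.

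**Step 1: what the weekday rule fixes.** Seven nights from Sunday evening end in the mornings of Monday to Sunday. Take a pupil with a five-day school week. In a full term week, 5 of 7 accelerometry mornings and 3 of 3 saliva mornings are school mornings. In a full holiday week the counts are 0 of 7 and 0 of 3. Both weeks satisfy the rule. The saliva days are the more exposed, because they contain no weekend morning that is free in both kinds of week.

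**Step 2: what could balance week type.** Recruitment runs from 1 February 2021 to about February 2022, so both kinds of week occur. The luteal-phase rule concerns the cycle, not the school calendar. None of the three matching factors concerns the calendar. No stated feature of the design does the balancing.

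**Step 3: size, under assumptions.** The documents give neither the effect of a free schedule on any outcome nor the share of free weeks in each group. Both are assumed.

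- Bias in SD units: d = Δp × s, where Δp is the group difference in the share of free weeks and s is the schedule effect in SD of the outcome.
- Rejection rate with no effect of depression: two-sided t test at 5%, 30 per group, 58 degrees of freedom, noncentrality d × √(30/2) = d × √15.

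Each cell gives d, then the rejection rate:

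| Δp | s = 0.3 | s = 0.5 | s = 0.8 | s = 1.0 |
|---|---|---|---|---|
| 0 | 0; 0.050 | 0; 0.050 | 0; 0.050 | 0; 0.050 |
| 0.20 | 0.06; 0.056 | 0.10; 0.067 | 0.16; 0.094 | 0.20; 0.119 |
| 0.50 | 0.15; 0.088 | 0.25; 0.159 | 0.40; 0.332 | 0.50; 0.478 |

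Example: Δp = 0.20 and s = 0.5 give d = 0.10, noncentrality 0.10 × 3.87 = 0.39 and a rejection rate of 0.067.

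**Step 4: imbalance by chance alone.** Suppose each participant, in either group, has the same probability of a holiday week. A difference of at least 6 of 30 (20 points) then has probability 0.05, 0.10 or 0.14 when that probability is 15%, 25% or 35% (two independent binomials). Chance is already included in an ordinary 5% test, so this adds no bias on average. It shows that a 20-point imbalance in the realised sample would not be remarkable at this size.

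**The case against.** The case on the other side is substantial, and much of it stands.

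- **Silence in a condensed article.** The weekday sentence is true and does not claim that mornings are comparable. Which weeks can be booked may be set out in the full protocol, and covariates may be in an analysis plan. A reader might infer that term and holidays are ignored. The documents do not say so; they show only that the stated rule does not deal with them.
- **Much can be recovered.** A reader might infer that schedule cannot be separated afterwards. That is too strong. The start date of each week is known and the study has one centre, so term or holiday status can largely be looked up. Actual sleep and wake times are recorded daily, and usual times for both regimes are collected at baseline. What the described morning questionnaire does not capture is the type of day actually lived, such as an absence on a school day.
- **Already a limitation.** Strengths and limitations concedes that external influences at home cannot be controlled and defends everyday conditions. This answers only part of the point: week type can be scheduled and recorded, and a difference between groups is not mentioned there.
- **Adjustment has traps.** Controls with any history of psychiatric intervention are excluded, so only patients can have clinic days. As a covariate, clinic attendance could not be separated from group. Wake time or school absence may itself result from depression, so adjusting for it could remove part of the effect sought.
- **Term-only scheduling has a price.** The article relies on prompt appointments to reach patients before medication or admission is decided, and antidepressant medication is an exclusion criterion. Delaying patients could lose them.

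**Conclusion.** The point holds as a design weakness that is cheap to reduce. By weekday and cycle phase alone, the stated rule leaves term and holiday weeks free to fall unequally between the groups. Differences in sleep and in the cortisol awakening response could then partly reflect schedule. The size is unknown: zero with balanced week types, small for modest imbalances (d up to 0.20 at 20 points over the assumed effects), and serious only if a large imbalance meets a large schedule effect.

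Two stronger readings are not supported.

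- **A false-positive rate near 21%.** Assume waking is 2 h later on free days, the SD within day type is 1 h, and holiday weeks make up 15% of one group and 35% of the other (mean 25%). The SD is √(1 + 4 × 0.25 × 0.75) = 1.32 h, the difference is 2 × 0.20 = 0.4 h, d = 0.4/1.32 = 0.30, and the rejection rate is about 0.21. The arithmetic is right, but every input is assumed and the result concerns wake time, which Primary outcome does not name.
- **Extra variance in every primary outcome.** The background section on interrelations cites an association of sleep duration with cortisol levels, not with the awakening increase. The same study found no significant association of sleep duration with alpha-amylase at awakening.

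**What to change.** 1. Under Physiological consistency of measurement, add that, where feasible, each control's measurement week is placed in the same kind of week (term or holiday) as that of the matched patient. Leave patients' appointments as prompt as they are now; do not restrict patients to term weeks.
2. Add one item to the morning questionnaire: school or work, clinic, or free day. Also derive term or holiday status from the calendar dates, which covers participants measured before the change.
3. Prespecify a sensitivity analysis of the sleep and hormone comparisons adjusted for term versus holiday week, and report week type by group.
4. Handle clinic attendance descriptively, or by a sensitivity analysis without day patients, and not as a covariate.

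The cost is one questionnaire item and less flexibility in scheduling controls, whose start dates are already limited by the Sunday rule and, for female participants, the luteal phase.

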#### Secondary outcome

The secondary outcome of our study is the examination of the severity of depressive symptoms, further psychopathologies, and stress responsiveness at the first study appointment and its relation to sleep quality.

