#### *A priori* power calculation

*A priori* sample size was calculated with the program G*Power version 3.1.9.4,^61^ based on a previous study by Schmidt et al^14^ with a medium effect size of *f* = 0.30, an *α* error probability of 0.05 and two groups. To investigate group differences in the CAR through a repeated measures analysis of covariance (ANCOVA), a total of 28 participants would be required to achieve a power of 80%. In accordance with Selvi et al, we assume a medium effect size of *d* = 0.40 for correlational analyses of sleep quality and depressive symptoms.^62^ A sample size of *N* = 44 was deemed necessary for statistical power of 80%. Finally, to enable the calculation of a direction-dependence analysis in case of non-normally distributed and sufficiently skewed data,^63^ we will include a sample of *N* = 60 participants: 30 participants with a depressive disorder and 30 healthy participants as parallel controls.

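### The depression score is taken once, at T1, but girls' measurement weeks wait for the luteal phase, so it can precede the accelerometry, diary, SF-A/R and saliva data by weeks and weaken those correlations

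*Protocol article*

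**What the plan says.** Four statements in the protocol article have to be read together.

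- **When the score is taken.** The section on assessment of depressive symptoms places the BDI-II at T1 and gives its look-back: "Frequently observed symptoms are inquired for the past 2 weeks in 21 items". One item is dropped for this sample, leaving 20. The text describes no second BDI-II, although there is a second appointment (T2) at which devices and samples are returned.
- **When the cycle is known.** Under Physiological consistency of measurement: "Start of the most recent menstruation is assessed at the first study appointment".
- **How the week is placed.** The same section says that "all measurements are scheduled for the female participants" luteal phase. Every participant starts on a Sunday evening. No further timing rule is stated for boys.
- **How the score is used.** The secondary outcome takes severity "at the first study appointment and its relation to sleep quality". The Statistical analysis section plans bivariate correlations, with false discovery rate correction, between subjective and objective sleep quality, depressive symptoms and the cortisol and alpha-amylase increase.

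The SF-B/R, a sleep questionnaire, is also completed at T1 and covers the previous two weeks.

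**The concern.** Because the cycle is first asked about at T1, T1 cannot itself be timed from that answer. It is the measurement week that moves. A girl seen at an unsuitable point in her cycle answers the BDI-II about one fortnight and is measured in a later one. A boy waits only for the next Sunday.

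A correlation between a score and sleep or saliva data from a later week is expected to be smaller than one from the same period, by an amount that depends on how far symptoms shift in between. In the index group they may well shift: patients come from an active out-patient and day-patient service, and the section on adverse events says that indicated treatment is not postponed for the study. At stake are the severity correlations with accelerometry, the daily questionnaire, the SF-A/R and the salivary markers. The loss would differ between girls and boys.

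**Working it through.** **1. The plan's own figure.** The power section uses an "error probability of 0.05 and two groups", an effect of "0.40 for correlational analyses of sleep quality and depressive symptoms", and states that N = 44 "was deemed necessary for statistical power of 80"%. The 0.40 is labelled d, but N = 44 reproduces only if it is read as a correlation. With two-sided alpha 0.05 (sidedness is not stated) and a noncentral t:

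- ncp = √N × r/√(1 − r²) = √44 × 0.40/√0.84 = 2.895, giving power 0.807. N = 44 is the smallest N that reaches 0.80.
- The Fisher-z approximation gives N = 47. It is used below because it is simple and slightly conservative.

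The planned sample is "30 participants with a depressive disorder and 30 healthy participants as parallel controls", so N = 60.

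**2. Length of the wait.** Assumptions not in the documents: a 28-day cycle, luteal days 15 to 28, a random cycle day at T1, and T1 on any day from Monday to Friday.

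- *Next Sunday only (boys).* Waits are 6, 5, 4, 3 or 2 days: mean 4, maximum 6.
- *Girls, all seven nights luteal.* The first night must fall on days 15 to 22. By cycle day of the first available Sunday, the extra wait is 0 days for days 15–22 (8 of 28), 7 for days 8–14 (7 of 28), 14 for days 1–7 (7 of 28) and 21 for days 23–28 (6 of 28). Mean extra = (7×7 + 7×14 + 6×21)/28 = 9.75, so the mean wait is 4 + 9.75 = 13.8 days and the maximum 6 + 21 = 27. The wait exceeds 14 days in 13/28 = 46%.
- *Girls, only the first night luteal.* Days 15–28 need no extra wait. Mean extra = (7×7 + 7×14)/28 = 5.25, so the mean wait is 9.3 days and the maximum 6 + 14 = 20. The wait exceeds 14 days in 7/28 = 25%.
- *Other cycle lengths.* For cycles of 26 to 35 days the mean runs from 8.6 to 17.2 days and the maximum from 20 to 34, over both readings.

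**3. Effect on the correlation.** Let s be the stability of the score over the gap. Then r_obs = 0.40 × s, and power = Φ(atanh(r_obs) × √57 − 1.96) at N = 60. With no gap, atanh(0.40) = 0.4236, times 7.550 is 3.198, less 1.96 is 1.238, and Φ = 0.892.

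| Assumed stability s | r_obs | Power at N = 60 | N for 80% |
|---|---|---|---|
| 1.00 | 0.40 | 89% | 47 |
| 0.95 | 0.38 | 86% | 53 |
| 0.90 | 0.36 | 81% | 59 |
| 0.85 | 0.34 | 76% | 66 |
| 0.75 | 0.30 | 65% | 85 |

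These rows apply the loss to all 60 participants. If only girls are affected, with an assumed share of 0.67, then r_obs = 0.40 × (0.67s + 0.33). For s = 0.90 this is 0.373 and power is 84%; for s = 0.75 it is 0.333 and 74%.

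**The case against.** A reader might infer that power drops to 65%, since the protocol gives a BDI-II retest reliability of at least 0.75. The documents do not support that as the expected loss. The value is a lower bound with no stated retest interval. A retest coefficient also mixes questionnaire error with real change, and the planning value of 0.40, taken from a previous study, presumably already contains questionnaire error. Setting the internal consistency of at least 0.84 against it leaves roughly 0.75/0.84 = 0.89, hence r = 0.357 and power of 80.5%. This is only approximate, because both inputs are lower bounds. The 65% also spreads to everyone a lag that the rule creates for girls.

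A reader might also infer that every sleep–severity correlation is affected. It is not: the SF-B/R shares T1 and the two-week window with the BDI-II, and the secondary outcome does not name a particular week of sleep.

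Nor is the primary group comparison biased by the rule. Controls are matched by gender, so the same scheduling applies in both groups, and group membership rests on diagnosis, not on the T1 score. Pooling depressed and healthy adolescents also makes much of the score's variance between-group and probably stable. The loss would matter more within the index group, where at n = 30 power is about 60% at r = 0.40 even without a gap.

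Finally, the luteal rule has a stated reason, comparability of the cortisol response between the sexes. The study-schedule figures, not available here, may give a maximum interval. A cap would shorten the gap but not remove it. These points limit size and scope; the mechanism stands.

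**Conclusion.** The point holds in a limited form. The stated timing rules separate a girl's only described BDI-II score from her measurement week by about 9 to 14 days on average and up to 20 to 27 days, against about 4 and at most 6 days for a boy. The expected effect is attenuation, unequal by sex, of the correlations between depressive symptoms and accelerometry, diary, SF-A/R and saliva measures.

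The size of the loss cannot be fixed from the documents. At stability of 0.90 or better, the planned 60 participants still give about 80% power or more; 65% is a worst case. The result rests on assumed cycle and luteal lengths, the weekday of T1, the share of girls, the stability of the score, and 0.40 being a correlation. This is an inexpensive improvement to a secondary analysis and not a flaw in the main comparison.

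**What to change.** Repeat the 20-item BDI-II at T2 for all participants, boys included. Hold T2 within seven days of the last night, so that the two-week look-back covers all seven nights (7 + 7 = 14 days). Use the T2 score in the correlations with accelerometry, daily diary, SF-A/R and saliva, and keep the T1 score for the SF-B/R. The luteal scheduling can stay as it is.

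For participants already measured, report the interval from T1 to the first night by sex and group. Test whether the correlation varies with it through a score-by-lag interaction, as a sensitivity analysis only and read with caution because lag is tied to sex. Entering lag merely as a covariate would not undo attenuation. Restricting to lags of 14 days or less could discard up to 46% of the girls under the assumptions above.

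The cost is a few minutes of questionnaire at an existing appointment and a second score to report.
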